## Abstract

**Background:**

Dental caries remains a significant public health problem, prevalence being linked to social and economic deprivation. Occlusal surfaces of first permanent molars are the most susceptible site in the developing permanent dentition. Cochrane reviews have shown pit and fissure sealants (PFS) and fluoride varnish (FV) to be effective over no intervention in preventing caries. However, the comparative cost and effectiveness of these treatments is uncertain. The primary aim of the trial described in this protocol is to compare the clinical effectiveness of PFS and FV in preventing dental caries in first permanent molars in 6-7 year-olds. Secondary aims include: establishing the costs and the relative cost-effectiveness of PFS and FV delivered in a community/school setting; examining the impact of PFS and FV on children and their parents/carers in terms of quality of life/treatment acceptability measures; and examining the implementation of treatment in a community setting.

**Methods/design:**

The trial design comprises a randomised, assessor-blinded, two-arm, parallel group trial in 6–7 year old schoolchildren. Clinical procedures and assessments will be performed at 66 primary schools, in deprived areas in South Wales. Treatments will be delivered via a mobile dental clinic. In total, 920 children will be recruited (460 per trial arm). At baseline and annually for 36 months dental caries will be recorded using the International Caries Detection and Assessment System (ICDAS) by trained and calibrated dentists. PFS and FV will be applied by trained dental hygienists. The FV will be applied at baseline, 6, 12, 18, 24 and 30 months. The PFS will be applied at baseline and re-examined at 6, 12, 18, 24, and 30 months, and will be re-applied if the existing sealant has become detached/is insufficient. The economic analysis will estimate the costs of providing the PFS versus FV. The process evaluation will assess implementation and acceptability through acceptability scales, a schools questionnaire and interviews with children, parents, dentists, dental nurses and school staff. The primary outcome measure will be the proportion of children developing new caries on any one of up to four treated first permanent molars.

**Discussion:**

The objectives of this study have been identified by the National Institute for Health Research as one of importance to the National Health Service in the UK. The results of this trial will provide guidance on which of these technologies should be adopted for the prevention of dental decay in the most susceptible tooth-surface in the most at risk children.

**Trial registrations:**

ISRCTN ref: ISRCTN17029222 EudraCT: 2010-023476-23 UKCRN ref: 9273

## Background

Despite the decline in the prevalence of dental decay in the United Kingdom in the last three decades, 57% of 15 year-olds still have dental caries (tooth decay) sufficiently severe to require a filling or extraction [1]. Dental caries is uneven in its distribution in the population and has been shown by numerous studies to be closely linked to social and economic deprivation [2], with a three-fold difference in disease burden from most to least deprived [3]. Within the mouth, the majority of detected incremental decay is to be found on the pit and fissure surfaces of molar teeth in children [4] and adults [5]. These facts dictate the need for caries-prevention technology, targeted at the most susceptible tooth surfaces in the most susceptible members of the population. Two competing technologies have the potential to fulfill this role, pit and fissure sealants and fluoride varnishes.

Pit and fissure sealants comprise a Bis-GMA resin, which is applied to the occlusal surface of the tooth using acid-etch technology. They work by physically obliterating the pit and fissure system which harbours cariogenic organisms and thereby inhibit the initiation of caries. First developed in the 1960s, they are an established technology and widely used in clinical practice. Numerous studies have investigated the clinical effectiveness of fissure sealants and this has been the subject of a Cochrane review. A meta-analysis of seven studies comparing sealed teeth to untreated controls demonstrated caries reductions ranging from 87% at 12 months to 60% at 48–54 months [6].

Fluoride varnishes have also been marketed since the 1960s and comprise a topical medication which is painted onto the tooth surface. They contain a high concentration of fluoride (22,600 ppm) and are licensed for application by dental professionals. The varnish forms a quick-setting base which subsequently releases fluoride. Fluoride acts to prevent caries by inhibiting the demineralisation and encouraging the remineralisation of dental enamel. A Cochrane review suggested a pooled prevented fraction estimate of 46% (95%CI 30%-63%) when fluoride varnish is tested against no treatment controls [7].

In relation to the cost-effectiveness of technologies in this field, the evidence base is generally sparse with relatively few attempts to assess the relative worth of techniques to prevent dental decay. Those that have been undertaken tend to suffer from design and methodological flaws. However, one US study [8] assessed the 4-year incremental cost-utility of sealing first permanent molars, compared with non-sealed molars, of 6-year-olds from a societal perspective and identified the group of teeth or children in whom sealants are most cost-effective. They concluded that sealants improved overall utility of first permanent molars after 4 years; that the cost-utility ratio of sealing the first permanent molar varied by arch and type of utilisers; and that sealing first permanent molars in lower dental utilisers was the most cost-effective approach for prioritizing limited resources. However, this study was a comparison between sealing and non-sealing, as opposed to a comparison between different preventive technologies. Thus, while the clinical effectiveness of the technologies (PFS and FV) as caries-preventive measures is established when compared to no treatment controls, a significant question remains unanswered: What is the relative clinical and cost-effectiveness of these technologies when compared to each other?

The application of PFS in particular is an involved procedure, the success of which is dependent on clinical delivery in a dental-chair. The acid-etch necessary for their long-term adherence to the tooth surface is critically dependant on maintaining a dry-field during application. The clinical technique involves the use of rotary dental instruments to clean the tooth surface, suction devices and a compliant patient. In contrast, FV application simply involves drying the tooth and painting with a brush/applicator. FV can be applied by less skilled dental personnel (nurses) whereas PFS requires the involvement of a dentist or dental hygienist. If FV were proven to be an acceptable alternative to PFS (in terms of clinical, cost and patient acceptability criteria) then the potential benefits in terms of health improvement and the effective and efficient delivery of services would be enormous.

Preventive dental methods can be very effective in reducing tooth decay in children. A recent Cochrane review has compared the effectiveness of pit and fissure sealants with fluoride varnishes in the prevention of dental decay on occlusal surfaces [9]. Hiiri and colleagues concluded that while there was some evidence of the superiority of PFS over FV in occlusal decay prevention it remains unclear to what extent there is a difference between the effectiveness of PFS and FV [9]. Importantly from the perspective of the National Health Service (NHS) in the United Kingdom, there is insufficient evidence on which to make recommendations for clinical practice and which (PFS or FV) represents the most effective technology. The review did not specifically address the relative efficiency of the technologies.

There is therefore good quality secondary research evidence which has identified the need for the study described in this protocol.

From a societal perspective, the cost of treating dental caries poses a substantial burden on dental services and individuals throughout life. Avoiding the pain and suffering associated with dental caries is desirable, as is avoiding the impact of dental disease on the quality of life of affected individuals. Dental restorations in permanent teeth in childhood require maintenance throughout life. The outcome of this trial has the potential to benefit both those participating and, by extrapolation, the one in three children in Great Britain who have experienced dental decay by eleven years of age.

The Community Dental Service (CDS) of Cardiff and Vale University Health Board provides preventive dental care to children attending primary schools in areas of social and economic deprivation under the Welsh Government’s “Designed to Smile” programme. Under this programme Mobile Dental Clinics (MDCs) visit schools at regular intervals. This programme provides the vehicle for delivery of this trial.

### Trial aim

The overall aim of the study is to identify and compare the relative clinical and cost-effectiveness of two established technologies, pit and fissure sealants (PFS) and fluoride varnish (FV) for the prevention of dental caries in first permanent molar teeth in children aged 6–7 years.

### Trial objectives

The objectives of the SoV trial are as follows:

#### Primary objective

To compare the clinical effectiveness of PFS and FV in preventing dental caries in first permanent molars in 6–7 year-olds, as determined by:

• The proportion of children developing new caries on any one of up to four treated first permanent molars

• The number of treated first permanent molar teeth caries-free at 36 months

#### Secondary objectives

• To establish the costs and budget impact of PFS and FV delivered in a community/school setting and the relative cost-effectiveness of these technologies

• To examine the impact of PFS and FV on children and their parents/carers in terms of quality of life/treatment acceptability measures.

• To examine the implementation of treatment in a community setting with respect to the experience of children, parents, schools and clinicians.

## Methods/design

### Study design

This is a randomised, assessor-blinded, two-arm, parallel group trial in 6–7 year old children. A total of 920 participants will be randomised to receive either PFS or FV. Clinical procedures and assessments will be performed at approximately 66 schools in South Wales via the use of a mobile dental clinic.

The trial schema is shown in Figure 1.

**Figure 1 F1:**
[figure not shown]
Trial Schema.

### Setting and study participants

The target population is children aged 6–7 years attending primary schools in areas of social and economic deprivation. All children in these schools are deemed at high caries-risk according to Scottish Intercollegiate Guidelines Network (SIGN) [10] /British Society of Paediatric Dentistry (BSPD) guidelines [11] and qualify for PFS/FV application. With parental consent and child assent, children aged 6–7 years who have at least one erupted non-carious first permanent molar tooth will be randomly allocated to receive either PFS or FV.

### Participant selection

Children will be considered eligible to join the trial if they meet all of the following inclusion criteria and none of the exclusion criteria. Certain inclusion and exclusion criteria (where identified) require evaluation by a dentist during a baseline clinical examination. Only children that are considered to meet all other inclusion/exclusion criteria will undergo a baseline clinical examination.

#### Inclusion criteria

• Children aged 6–7 years, attending the schools participating in the current Cardiff and Vale University Health Board “Designed to Smile” Programme

• Children for whom the person with parental responsibility has provided written informed consent

• Children with at least one fully-erupted caries-free first permanent molar (determined at baseline examination)

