#### Fluoride varnish (FV)

The FV used for evaluation in the study is Duraphat® 50 mg/ml dental suspension (Colgate-Palmolive (UK) Ltd; PL 00049/0042), equivalent to 22,600ppm fluoride. We chose this product as a commonly used FV and that used in the existing community dental programme. FV will be supplied as 10 ml tubes for multiple applications and applied topically as a thin layer to the pits, fissures and smooth surfaces of eligible teeth. As per the Duraphat Summary of Product Characteristics (SmPC), dosage per single application will not exceed 0.4 ml.

Initial application of FV will occur within 2 weeks of the baseline dental examination, and will be performed by a suitably qualified and trained dental hygienist according to the conventional clinical protocol established by the CDS. FV will be re-applied at 6, 12, 18, 24, and 30 months.

All applications of FV will be documented on a treatment record form, which will capture the date, batch number, patient ID number and number of applications (i.e. teeth) performed.

Where children enrolled onto the study are registered with a General Dental Practitioner (GDP), the GDP will be informed of the child’s participation in the study and requested to not apply either PFS/FV (or other fluoride-based treatment) for the duration of the trial.

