### Clinical evaluation

Participants will undergo a clinical examination using standard visual caries diagnosis (both enamel and dentinal level) at baseline and 12, 24 and 36 months by a trained and calibrated dentist, blind to treatment allocation. All fully-erupted non-carious first permanent molars (FPM) will be treated.

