### Secondary outcome measurement

Patient rated treatment acceptability will be measured using the Delighted-Terrible (D-T) faces scale. This scale consists of five items rated 1–5 relating to the participants experience of treatment. The D-T scale score will be calculated as the sum of valid responses for individual items divided by the number of valid responses.

The hygienist and nurse rated treatment acceptability will be measured using the Adverse Outcomes (A-O) scale. This scale consists of 6 items scored 0–1. The A-O scale score will be calculated as the sum of valid responses for individual items divided by the number of valid responses.

The retention of sealants in the sealant arm will be derived from the treatment records. The proportion of sealants retained intact and partially intact will be reported at 1 year, 2 years and 3 year time points.

The presence and severity of hypomineralisation/hypoplasia in the first permanent molars will be recorded at each dental examination and the prevalence reported by treatment arm. Severely hypoplasic teeth will be excluded from the trial.

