### Time plan for the SoV trial

Participant recruitment began in July 2011 and is planned to continue to until December 2012. Children will be followed up for three years and therefore the last child will have their final follow-up assessment in December 2015.

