## Discussion

The study will be conducted in primary schools in South Wales. Under the umbrella of the Welsh Oral Health Action Plan, the Community Dental Service (CDS) in Cardiff and Vale University Health Board delivers a primary school based PFS placement programme (‘Designed to Smile’) to approximately 3,300 6 year-olds annually. This programme, and its predecessor, have been in place since 2002. The programme involves Community First Schools, so designated by the Welsh Government on the basis of the high socioeconomic deprivation status of the school catchment area. The prevalence of dental caries in these areas is amongst the highest in the United Kingdom [31]. Permission to adapt the Designed to Smile programme for the purposes of this trial has been granted by the Chief Dental Officer for Wales.

A schools-based programme, utilising mobile dental clinics, is considered to have several advantages over conducting the proposed research in general dental practices.

The Designed to Smile programme is established and gives access to a cohort of high-risk children, experiencing the necessary burden of disease to allow an appropriate test of the technologies. This setting accesses children who might not otherwise routinely attend a general dental practice - attendance being linked to socioeconomic status [32]. In addition to having the necessary throughput of patients to achieve the required recruitment rate of at-risk children (as defined by SIGN / BSPD guidelines [10,11]), a schools-based setting will facilitate control over retention and follow-up. Furthermore, and perhaps most importantly, the CDS has established a relationship with the schools, parents and the children over many years which will obviously facilitate meaningful user and participant involvement in the study. In addition to service user representatives, staff involved in the existing CDS programme were consulted during the design and work-up of this trial, ensuring that it will be implemented and conducted in a way that is empathetic to the needs of the participating children, their parents and their schools.

On the basis that we are testing the relative clinical and cost-effectiveness of two established technologies, both of which have been proven clinically effective against placebo treatments [6,7], this trial will not contain a placebo control arm.

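### The eligibility rule does not require study molars to be unsealed at baseline, so varnish-arm children may enter with the comparator already on their study teeth

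*Protocol article*

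**What the plan says.** **Who and which teeth.** The only tooth-related inclusion criterion is "Children with at least one fully-erupted caries-free first permanent molar (determined at baseline examination". The section on setting and study participants gives the same rule in other words. None of the seven exclusion criteria concerns an existing sealant. Under Clinical evaluation the article adds: "All fully-erupted non-carious first permanent molars (FPM) will be treated". The one tooth-level exclusion appears under Secondary outcome measurement: "Severely hypoplasic teeth will be excluded from the trial".

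**Where the children come from.** They are aged 6–7 and "attending the schools participating in the current Cardiff and Vale University Health Board “Designed to Smile” Programme". According to the Discussion, the health board's dental service "delivers a primary school based PFS placement programme (‘Designed to Smile’) to approximately 3,300 6 year-olds annually". It adds: "This programme, and its predecessor, have been in place since 2002". The time plan states: "Participant recruitment began in July 2011 and is planned to continue to until December 2012".

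**Protection against non-trial sealant.** Where a child is registered with a general dental practitioner, that practitioner is "requested to not apply either PFS/FV (or other fluoride-based treatment) for the duration of the trial".

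**Design and model.** Randomisation is stratified by school and minimised on gender and baseline caries. The primary model adjusts for gender, baseline caries and number of designated study teeth. Prior sealant appears in neither.

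**The concern.** The primary objective is a head-to-head comparison of sealant and varnish. The host programme was running before the trial opened. A 7-year-old recruited in 2011 or 2012 could have been sealed at age 6 on a previous programme visit, or by a practitioner. Followed literally, the eligibility text admits that child and makes the sealed molars study teeth. In the varnish arm, varnish then goes over an existing sealant and the result counts as varnish.

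The effect falls on one side of the contrast. Earlier sealing gives a varnish child some of the comparator's occlusal protection, but gives little extra to a sealant child who would have been sealed anyway. Randomisation spreads prior sealing evenly between arms without removing this dilution. What is at stake is a smaller observed difference, and hence a greater chance of missing a real one.

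**Working it through.** **1. Inputs.** From Sample size considerations: 3-year caries incidence of 30% (varnish) and 20% (sealant), 80% power, 5% significance, at least 313 per group, 920 randomised, 8% annual loss, 5% absence at the final examination, 680 analysed (340 per arm). Two-sided testing is assumed because the article does not state sidedness. The share of children already sealed, s, is not given and is an assumption.

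**2. Reproducing the plan's figures.**
- Pooled-variance formula: n' = [1.96·√(2·0.25·0.75) + 0.8416·√(0.20·0.80 + 0.30·0.70)]² / 0.10² ≈ 293.2.
- With continuity correction: n = (n'/4)·[1 + √(1 + 4/(n'·0.10))]² ≈ 312.8, so 313. This matches.
- Attrition: 920 × 0.92³ = 716.4, a loss of 203.6 (stated 204). Then 716.4 × 0.95 = 680.6 (stated 680). This matches.

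The sample size arithmetic is not in question.

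**3. Dilution.** Let a fraction s of varnish children have every study molar sealed and carry the full sealant-arm risk. Then:
- varnish rate = 0.30·(1 − s) + 0.20·s = 0.30 − 0.10·s
- sealant rate held at 0.20
- power = Φ(difference / SE − 1.96), with SE = √[(0.20·0.80 + p·(1 − p))/340] and p the varnish rate

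For s = 10%: p = 0.29, SE = √(0.3659/340) = 0.0328, 0.09/SE = 2.743, and Φ(0.783) = 78.3%.

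| s | Varnish rate | Difference (points) | Power, unpooled | Power, pooled |
|---|---|---|---|---|
| 0 | 30.0% | 10.0 | 85.8% | 85.5% |
| 5% | 29.5% | 9.5 | 82.3% | 82.0% |
| 10% | 29.0% | 9.0 | 78.3% | 78.0% |
| 20% | 28.0% | 8.0 | 68.9% | 68.6% |

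**4. Where the planned 80% is lost.** With the unpooled formula, s = 8% gives p = 0.292 and power of 80.0%. With the continuity-corrected formula that reproduces 313, s = 5% already needs 344 per arm, slightly above the 340 expected.

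**5. Weaker protection.** If an existing sealant carries only a fraction k of the trial sealant's benefit, the varnish rate is 0.30 − 0.10·s·k. With s = 20% and k = 0.5 the rate is 29.0% and power is 78.3%, the same as s = 10% with full benefit.

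**The case against.** **Tooth-level rules may sit elsewhere.** The eligibility lists concern children. Severe hypoplasia shows that the article puts at least one tooth exclusion outside them, and designated study teeth are mentioned without a designation rule. The full protocol might deal with sealed molars. That is possible, but the article does state which teeth are treated, under Clinical evaluation, and that sentence covers all fully erupted non-carious first permanent molars. The gap is therefore in a stated rule.

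**The number exposed may be small.** A reader might infer that about 3,300 children a year were sealed. The Discussion says the programme is delivered to that many; it does not say how many received a sealant. About 40% of consented children are expected to lack an erupted first permanent molar, so many could not have been sealed earlier. The programme was adapted to deliver the trial, and the 3,560 planned invitations are close to one annual intake. This suggests, without proving, that many children are met when the programme would first treat them. These points stand, and they leave s unknown.

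**The power figures lean high.** They need every study molar of an affected child to be sealed and as well protected as in the trial's sealant arm. Trial sealants are checked every six months, re-applied when needed and extended to newly erupting molars; an earlier sealant in a varnish child is not described as receiving any of this. The outcome is caries on any of up to four molars, so a partly sealed child keeps the risk from the others. This stands too.

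**Bias between arms.** A reader might infer that prior sealing makes the arms unequal. It precedes a randomisation stratified by school, so the documents support dilution only, not systematic imbalance.

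**Conclusion.** The point holds as a gap in the stated eligibility rule. Sealed, sound molars qualify as study teeth, the source schools host a sealant programme, and no described safeguard covers sealant placed before enrolment. The direction of the effect is towards no difference.

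Its size is unknown. The drop from about 86% power to 82%, 78% or 69% at s = 5%, 10% or 20% rests on an assumed s, full sealant-arm protection on all study molars, and a sealant arm unchanged at 20%. It illustrates roughly the most that a given s would cost and is not a forecast. The documents do not support the conclusion that the trial is underpowered. They support only that it is open to avoidable dilution of unstated extent.

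**What to change.** Under Setting and study participants, Inclusion criteria and Clinical evaluation, define a study tooth as a first permanent molar that is fully erupted, caries-free and without an existing sealant at the baseline examination, before randomisation. Require at least one such tooth per child. A molar already sealed at baseline would not be a designated study tooth in either arm; its clinical care is a separate matter for the investigators. The count of designated study teeth in the primary model should follow the same definition.

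If recruitment is complete, first establish whether the baseline charts recorded sealants. The sections on caries assessment and primary outcome measurement mention caries and caries treatment, not sealants at baseline. If the charts did record them, apply the rule identically to both arms, at least as a sensitivity analysis, and report by arm how many children and teeth were sealed at entry. The rule uses only information from before randomisation, so it does not introduce selection between arms.

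The cost is one phrase read off an examination that is already performed, plus the loss of a few otherwise eligible teeth or children.
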